## Abstract

**Background:**

Increased uptake of sodium is a major cause for cardiovascular disease and mortality. Reduction of daily salt intake below a reference level of 2 g per day (the equivalent to 5 g salt/day) is known to effectively reduce cardiovascular mortality. The widespread use of social media, with a constant increase in video consumption, is opening new avenues for the dissemination of innovative and scalable approaches to health-related information and recommendations for a healthy diet, such as via video interventions with short animated stories (SAS).

**Objective:**

This study will evaluate the effect of a sodium intake-SAS video intervention on immediate and medium-term knowledge about dietary sodium. Beyond that, immediate and medium-term effects on behavioral expectation to reduce sodium intake as well as voluntary post-trial engagement with the video content will be examined.

**Methods:**

In this 4-armed, parallel, randomized controlled trial, 10,000 adult, US participants will be randomly assigned to (1) a short, animated storytelling intervention video on sodium as a cardiovascular disease risk factor followed by surveys assessing the facts on sodium and cardiovascular disease conveyed in the video (2) the surveys only, (3) an attention placebo control video followed by the before mentioned surveys, and (4) an arm that is exposed to neither the video nor the surveys. Two weeks later, participants in all four arms will complete all of the surveys.

**Results:**

Primary outcomes are the immediate and medium-term effects of the short, animated storytelling intervention video on knowledge about dietary sodium. Secondary outcomes are immediate and medium-term effects of the short, animated storytelling intervention on behavioral expectation to reduce sodium intake as well as voluntary post-trial engagement with the video content.

**Conclusion:**

This study will extend the knowledge on the effects of short, animated storytelling for the containment of the global cardiovascular disease burden. Knowledge on the groups that may be more likely to voluntarily engage with SAS video content will help to improve targeting of future interventions towards audiences at risk.

**Trial registration {2a}:**

ClinicalTrials.gov NCT05735457. Registered on February 21, 2023.

**Supplementary Information:**

The online version contains supplementary material available at 10.1186/s13063-023-07418-6.

## Synopsis/World Health Organization Trial Registration Data Set {2b}

**Table Taba:** 

**Data category**	**Information**
Primary registry and trial identifying number {2a}	ClinicalTrials.gov (NCT05735457)
Date of registration in primary registry	February 21, 2023
Primary registry trial registration URL {2a}	https://www.clinicaltrials.gov/ct2/show/NCT05735457
Secondary identifying numbers	n/a
Source(s) of monetary or material support {4}	• The study is funded by an Alexander von Humboldt University [name] awarded to [name] [name]. • [name] is supported by a Berta-Ottenstein-Grant from the Faculty of Medicine, University of Freiburg.
Primary sponsor {5b}	Heidelberg University Hospital [name]
Secondary sponsor(s)	Not applicable.
Contact for public queries	[name], MPH University of Freiburg Medical Center Interdisciplinary Medical Intensive Care [name] Germany [contact] [contact] E-Mail: [contact]
Contact for scientific queries	[name], MPH University of Freiburg Medical Center Interdisciplinary Medical Intensive Care [name] Germany [contact] [contact] E-Mail: [contact]
Public title {1}	A short, animated storytelling video about sodium intake as a major cardiovascular risk factor and recommendations for a healthy diet: an online, randomized, controlled trial
Scientific title	A short, animated storytelling video to increase knowledge about sodium intake as a major cardiovascular risk factor and to give recommendations for a low-sodium healthy diet: an online, randomized, controlled trial
Countries of recruitment {9}	United States
Health condition(s) or problem(s) studied	High-sodium diet and excess sodium intake.
Intervention(s) {11a}	Short, animated storytelling video on sodium intake
	Short, animated attention placebo control video (content unrelated to information on sodium intake)
Key inclusion and exclusion criteria {10}	Participants (all genders) aged 18-59, that have registered with the Prolific Academic platform are eligible for this trial. No further in- or exclusion criteria apply.
Study type {8}	online, randomized, controlled four parallel-arm trial
Date of first enrollment	March 1^st^, 2023 (anticipated)
Target sample size {14}	10,000
Recruitment status	Not yet recruiting.
Primary outcome(s) {12}	Immediate and medium-term effects of the short, animated storytelling intervention video on knowledge about dietary sodium.
Key secondary outcomes {12}	Immediate and medium-term effects of the short, animated storytelling intervention on behavioral expectation to reduce sodium intake as well as voluntary post-trial engagement with the video content.

## Introduction

### Background and rationale {6a}

Cardiovascular diseases are the leadingcause of death globally. According to data from the Global Burden of Disease Study, an estimated 17.8 million people died from cardiovascular disease in 2017, representing about one third of all global deaths [1]. High systolic blood pressure and an unhealthy diet are the most relevant modifiable risk factors for cardiovascular disease and are supposedly responsible for more than 10 million deaths per year [2]. Increased uptake of sodium is a major cause for elevated systolic blood pressure with a presumed linear relationship between the amount of daily sodium consumption and systolic blood pressure [3]. In a modeling study, 1.65 million deaths from cardiovascular causes, that occurred in 2010, were attributed to sodium consumption above a reference level of 2 g per day (the equivalent to 5 g salt/day) [4]. Reduction of daily salt intake has been proven to effectively reduce elevated systolic blood pressure, major cardiovascular events, and mortality [5–7]. In a recently published cluster-randomized study, conducted in China, the rates of stroke, major cardiovascular events, and death were significantly reduced in participants who lowered their sodium intake by using potassium chloride as a salt substitute, compared with the group that consumed regular salt (sodium chloride) [7]. In a large UK population-based cohort study, always adding salt to foods (as compared to never or only rarely) was linked to a 28% higher risk of premature mortality and to 1.5 and 2.28 years lower life expectancy at the age of 50 years in women and men, respectively [6]. Consequently, the World Health Organization (WHO) recommends a low-sodium diet with salt intake of less than 5 grams per day for adults. Achieving this target could help to significantly reduce premature mortality and DALYs attributed to cardiovascular disease [8].

In the typical US diet, approximately 70% of an individual’s daily sodium intake comes from eating processed food, compared with only 5.6% from home-cooked meals [9]. Therefore, in order to achieve the WHO target, key steps involve increasing knowledge in the public about which foods are high in sodium and promoting behavioral shifts that help people to reduce their dietary sodium intake.

Video-based, short, animated, storytelling (SAS) has been introduced as a novel form of entertainment-education (E-E). In recent trials, it has been proven an effective strategy for health education and the promotion of beneficial health practices [10]. E-E videos may rapidly transfer knowledge to a wide audience through popular social media channels in a cost- and time-efficient manner. For this study, we designed a short (approximately 3.5 min long), animated storytelling video to convey basic knowledge about the importance of controlling and limiting the individual sodium consumption (see multimedia Appendix). This study will systemically evaluate the effectiveness of the SAS video approach to E-E by measuring the effect of our intervention on knowledge and behavioral expectation to reduce dietary sodium intake. The result will add to the literature on SAS video health education as well as informing future E-E video approaches aimed at conveying preventive health messages. Ultimately, the results of this study may inform the future design and implementation of population-based initiatives aimed at distributing knowledge and improving behaviors in support of healthier dietary choices.

### Objectives {7}

In this study, we aim toEvaluate the effect of SAS videos on knowledge about dietary sodium intake in the short- and medium-termEvaluate the effect of SAS videos on behavioral expectation to reduce sodium consumption in the short- and medium-termMeasure voluntary engagement with SAS video content

We hypothesize, that SAS videos help increase knowledge about dietary sodium intake in the short- and medium-term, but knowledge may decrease during the 2-week follow-up phase.

## Methods

### Trial design {8}

This study is a randomized-controlled parallel-group trial examining the effect of a short, animated storytelling video on knowledge and behavioral expectation to reduce dietary sodium intake. We will use an online academic research platform (Prolific Academic) to recruit and randomize 10,000 participants aged 18–59 years into four study groups.

In group 1 (intervention group), participants will be shown a SAS video on dietary sodium (see multimedia Appendix) and thereafter be asked to complete a questionnaire to assess knowledge on dietary sodium and behavioral expectation.

In group 2 (exposed control group), participants will be asked to complete a questionnaire to assess knowledge on dietary sodium and behavioral expectation (the same questionnaire as in group 1), however, without being exposed to the SAS video on dietary sodium before.

In group 3 (attention placebo control group), participants will be shown an attention placebo control (APC) video, unrelated to the outcomes measured in this trial, before being asked to complete the knowledge and behavioral expectation questionnaire.

Participants in group 4 (unexposed control group) will not view a video and will not be asked to complete the questionnaire.

Two weeks later, participants in all four arms will once again be asked to complete the knowledge and behavioral expectation questionnaire. Figure 1 illustrates the trial design.

**Fig. 1 Fig1:**
[figure not shown]
Trial design

### Study setting {9}

This study will be conducted purely online. Participants from the USA will be recruited and randomized through the platform Prolific Academic (ProA; https://www.prolific.co). The video intervention and questionnaires will be delivered to participants through the secure, online platform Gorilla, an experiment builder that provides users with the tools for undertaking online behavioral research (www.gorilla.sc).

### Participants and eligibility criteria {10}

ProA will recruit participants from its participant pool. Registered participants on the ProA platform must be between the ages of 18 and 59 years (all genders). For this trial, we will only recruit participants living in the USA. No further inclusion or exclusion criteria apply.

### Intervention description {11a}

The sodium intervention is a short, 2D animated storytelling video (3:09 min; https://youtu.be/QYqAbbifI9U). The video tells a humorous story about a man who dreams that his heart is threatening to quit on him. The heart character complains of being “under too much pressure” due to the amount of sodium in the man’s diet. Through this narrative, the heart character conveys foundational messages about the importance of consuming only the recommended amount of sodium, as well as how the man can change his behavior to reduce his sodium intake. The APC video is also a 2D animated storytelling video of similar length (3:29 min; https://youtu.be/LRiWQfLvQjQ) and serves as an attention placebo control. The video conveys general messages about hope and gratitude, through a fantasy story about an orange dragon who takes a group of children on a global journey. As in the intervention group, the video is shown to stimulate the subject's attention, but without conveying information related to sodium and cardiovascular risk. After watching these videos, the participants in both arms will complete a sodium questionnaire containing 30 questions and three behavioral expectation questions.

Participants can only complete the survey once.

### Explanation for the choice of comparators {6b}

At time point 1, knowledge scores and behavioral expectation will be compared between three groups that will receive the questionnaires (*Intervention Arm – Do-nothing Exposed Arm – Attention Placebo Arm*). This comparison is intended to find out the immediate effect on knowledge and behavioral expectation about sodium intake by watching the intervention video. The primary comparison will be between the *Intervention Arm* and the *Do-nothing Exposed Arm.* By comparing these groups with the *Attention Placebo Arm* we will also be able to eliminate a potential generalized attention-activation effect from watching an animated short film (unrelated to sodium).

At time point 2, comparing the *Intervention Arm* with the *Do-nothing Un-exposed Arm* will allow us to detect potential medium-term effects of watching the intervention video on knowledge and behavioral expectation — participants in the *Do-nothing Un-exposed Arm* will neither have been exposed to the intervention video nor the sodium knowledge questions at time point 1. At time point 2, comparing the *Do-nothing Exposed Arm* with the *Do-nothing Un-exposed Arm* will provide information about the effect of simply asking sodium-related questions on medium-term knowledge and behavioral expectation to reduce dietary sodium.

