#### Primary outcomes

For each participant, the overall score achieved in the sodium questionnaire will be calculated individually. The mean score for each study arm at time point 1 and time point 2 (i.e., re-assessment 14 days after entering the trial) will be calculated and compared between the *Intervention Arm*, the *Attention Placebo Arm*, and the *Do-nothing Exposed Arm* at time point 1 and between all four study groups at time point 2, using the *t*-test for two independent groups. We will also use multilevel regression analyses to control for demographic factors and other potential variables as needed. The analyses will be conducted using the R statistical software package (R 4.2.2).

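### The week-2 contrast that the protocol reads as the video's effect also contains the effect of having taken the questionnaire

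*Protocol article*

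**What the plan says.** The medium-term effect of the video on sodium knowledge is a primary outcome (Outcomes {12}). The section Explanation for the choice of comparators {6b} assigns a meaning to particular pairs of arms:

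- **Time point 1.** The primary comparison is Intervention versus Do-nothing Exposed. Attention Placebo is there to remove a general attention effect.
- **Time point 2, video.** Intervention versus Do-nothing Un-exposed "will allow us to detect potential medium-term effects of watching the intervention video on knowledge and behavioral expectation". The reason given is that participants in the Un-exposed Arm "will neither have been exposed to the intervention video nor the sodium knowledge questions at time point 1".
- **Time point 2, questioning.** Do-nothing Exposed versus Do-nothing Un-exposed "will provide information about the effect of simply asking sodium-related questions on medium-term knowledge and behavioral expectation to reduce dietary sodium".

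Trial design {8} sets out what each arm receives at time point 1. In the intervention group, "participants will be shown a SAS video on dietary sodium (see multimedia Appendix) and thereafter be asked to complete a questionnaire". The exposed control group completes "the same questionnaire as in group 1), however, without being exposed to the SAS video on dietary sodium before". "Participants in group 4 (unexposed control group) will not view a video and will not be asked to complete the questionnaire" at that time. Table 1 agrees with this.

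The Primary outcomes paragraph of the statistical methods {20a} plans t-tests of mean scores "between all four study groups at time point 2" and gives no pair priority.

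**The concern.** The two arms chosen to show the medium-term effect of watching the video differ in two respects at time point 1: the video and the questionnaire. Their week-2 difference is the sum of both effects. The protocol itself treats questioning as something that may change later knowledge, since it sets aside a separate contrast to measure it. The contrast that is said to show the video effect therefore includes a component that the protocol regards as distinct from the video.

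The attribution concerns a primary outcome. The comparator section is also the only place that says what the week-2 pairs mean. An analyst or author who follows it would report the combined effect as the effect of the video. The immediate effect would meanwhile be read from a pair in which both arms took the questionnaire. The Objectives section expects that knowledge may fall over the two weeks. If the immediate effect is read from one pair and the medium-term effect from the other, a testing effect enters only at week 2 and could mask such a fall.

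**Working it through.** **1. What each arm receives at time point 1** (Trial design {8}, Table 1)

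| Arm | Sodium video | Other video | Questionnaire |
|---|---|---|---|
| Intervention (I) | yes | no | yes |
| Do-nothing Exposed (E) | no | no | yes |
| Attention Placebo (A) | no | yes | yes |
| Do-nothing Un-exposed (U) | no | no | no |

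**2. What each week-2 contrast estimates.** Let T be the effect of having taken the questionnaire at time point 1, and V the effect of the sodium video among people who also took it.

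- I − U = V + T
- E − U = T
- I − E = V
- I − A = effect of the sodium video relative to the other video, with the questionnaire held constant

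The contrast named for the video, I − U, equals V only if T = 0.

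**3. Reproducing the protocol's sample size.** Inputs from Sample size {14}: d = 0.1, one-tailed type I error 0.01, power 80%.

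n = 2(z₀.₉₉ + z₀.₈₀)² / d² = 2(2.326 + 0.842)² / 0.01, which rounds up to 2008 per arm. The noncentral t version gives 2009, the stated figure. A two-sided 0.01 would need 2336, so the one-tailed reading of the inputs is the right one.

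**4. Rejection rate of I versus U when the video does nothing at week 2.** Set V = 0 and T = q in SD units. Completers per arm: 2500 × (1 − 0.20) = 2000. Then

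P(reject) = Φ(q·√(n/2) − 2.326), with √(2000/2) = 31.62.

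| Assumed q | q × 31.62 | minus 2.326 | P(reject), I versus U |
|---|---|---|---|
| 0 | 0 | −2.326 | 1.0% |
| 0.02 | 0.632 | −1.694 | 4.5% |
| 0.05 | 1.581 | −0.745 | 22.8% |
| 0.10 | 3.162 | 0.836 | 79.8% |
| 0.15 | 4.743 | 2.417 | 99.2% |

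A simulation of 20,000 trials at 2000 per arm gave 22.7% at q = 0.05 and 80.1% at q = 0.10 for I versus U. For I versus E it gave 0.9% to 1.1% at every q simulated (0, 0.05, 0.10 and 0.20), which is the nominal level.

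**5. Sensitivity**, for q = 0.02, 0.05 and 0.10:

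- All 2500 per arm retained, one-sided 0.01: 5.3%, 28.8% and 88.7%.
- 2000 per arm, two-sided 0.01: 2.7%, 16.0% and 72.1%.

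The level and sidedness come from the sample size section; the analysis section states neither. The values of q are assumptions, because the protocol gives no size for the testing effect.

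**The case against.** The strongest reply is that the remedy is already in the plan. The Primary outcomes paragraph compares all four arms at time point 2, which includes Intervention versus Exposed and Intervention versus Attention Placebo. The testing effect is also estimated separately, and (I − U) − (E − U) = I − E, so the planned arms do identify the video effect among people who took the questionnaire. This stands. The problem is one of label and priority, and no analysis is missing.

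It limits what may be inferred. Four stronger readings are tempting, and the protocol does not support them:

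- *That persistence cannot be judged.* Intervention versus Exposed is tested at both time points, as is Intervention versus Attention Placebo, so the same pair can be followed over time.
- *That a positive result cannot be attributed to the video at all.* That would hold only if Intervention versus Un-exposed were read alone, and the protocol does not say that it will be.
- *That the primary comparator is switched at week 2.* The protocol uses the word primary for a comparison only at time point 1 and names no primary pair at time point 2.
- *That the rates above are the trial's rate of false claims.* They belong to one contrast. Under the same null, the planned Intervention versus Exposed test rejects in 1% of trials and would expose the discrepancy.

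The objection also notes that the protocol describes no feedback of correct answers, so nothing in it supports a testing effect as large as 0.10 SD. That is fair, and it is why a range is shown. Finally, a comparison with an untouched control answers a legitimate question, namely video plus questionnaire against nothing.

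The objection does not remove the attribution itself. The one section that interprets the week-2 pairs gives the video effect to the pair that mixes two effects. No passage names a clean pair for it, and none says that the testing effect will be subtracted. This is an interpretation that the protocol states, so it is not a detail left to an analysis plan.

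**Conclusion.** The point holds as an error of attribution for a primary outcome. Intervention versus Do-nothing Un-exposed at time point 2 estimates the combined effect of video and questionnaire, and the protocol presents it as the effect of watching the video.

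The size depends on a quantity that the protocol does not give. With no true video effect at week 2, this contrast rejects in 4.5%, 23% or 80% of trials for testing effects of 0.02, 0.05 or 0.10 SD, and in 1% if testing has no effect. These figures assume 2000 completers per arm, a one-sided level of 0.01 and equal variances. The largest of the three testing effects equals the effect that the trial is powered to detect, so even a testing effect that is small by ordinary standards would matter here. The data needed for a clean reading will be collected and compared in any case.

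**What to change.** In Explanation for the choice of comparators {6b} and in the Primary outcomes paragraph of the statistical methods:

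1. Name Intervention versus Do-nothing Exposed at time point 2 as the primary contrast for the medium-term video effect, the same pair as at time point 1.
2. Name Intervention versus Attention Placebo at time point 2 as the supporting contrast.
3. Keep Exposed versus Un-exposed as the contrast for the testing effect.
4. Report Intervention versus Un-exposed only as the combined effect of video plus questionnaire.

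The cost is a change of wording and priority. Arms, data and sample size per arm stay as they are, because both contrasts use two arms of equal size. There are two downsides. The clean contrast may be smaller than the combined one. And since no arm sees the video without the questionnaire, the clean contrast estimates the video effect only among people who also took the questionnaire at time point 1; if the two interact, it may differ from the effect of the video alone. The report should state that limit.

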### Outcomes {12}

As primary outcomes, we will measure the immediate and medium-term effects of the short, animated storytelling intervention video on knowledge about dietary sodium. Secondary outcomes are the immediate and medium-term effects of the short, animated storytelling intervention on the behavioral expectation to reduce sodium intake as well as voluntary post-trial engagement with the video content.

